#### Others

*Pressure Pain Thresholds (PPT)*. Pressure pain thresholds will be assessed through a pressure algometer. The algometer will be applied to different points in the body (elbow and knee) and participants will be asked to indicate the point at which pressure changes to pain. The pressure will be gradually increased at approximately 1 kg/s until the participant indicates feeling pain. The threshold pressure at which the sensation changes from pressure to pain will be recorded in kilograms (kg) and used as an indicator of PPT. Higher PPT values indicate higher pain thresholds. The validity and reliability of using a pressure algometer to measure PPT have been established [53].

*Height and weight*. Both these variables will be determined by patient estimation, with no exploration of them in the measurement process.

*Sociodemographic*. This comprises Age, Marital status (Single, Married, Divorced, Widowed), Employment status (Active, Unemployed, Retired, Temporary disability, Student, Homemaker, Other), Educational level (none, primary, secondary, university), and Gender.

*Exercise*. Among the exercise variables, the parameters described below will be considered:

*Blood pressure and respiratory rate*. Measured with the Anura application, which has demonstrated reliability with a conventional blood pressure measurement of 98% [54].

*Saturation and HR* are Measured with an Oxylink finger pulse oximeter.

All the outcome measurements will be assessed in a random order at baseline, at the halfway point of the treatment, post-intervention, and one- and eight-months post-intervention (Figs 3–5).

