### Interventions

All patients who meet the inclusion criteria and agree to participate in the study will be informed verbally and in writing, with the delivery of the information sheet listing the specific characteristics of the study. They will be asked to sign the written informed consent form.

Sociodemographic data will then be collected, as well as psychosocial variables on their current pain process. This data collection will be carried out in a room in the physiotherapy gymnasium of the university center, previously designated for measurements by the evaluating researcher as well as blood extraction.

Once the specific questionnaires and the pressure pain threshold (PPT) at the joints of the elbow and tibialis anterior are measured, a trained professional will collect 5 ml of blood from the ulnar vein of the participants in a citrate vacutainer. The blood collection will always take place between 6 p.m. and 7 p.m., to minimize the possible effects of circadian changes [37–39]. Blood samples will be collected in tubes containing K3-EDTA and centrifuged at 1000 g for 10 min at 4°C. The supernatants for the total plasma (TP) condition will be frozen at -80°C. Blood collection will be performed in both groups at rest before the intervention, 15 days after the intervention, at the end of the intervention period, and at 1 month and 8 months after the intervention.

After the initial data collection, a researcher other than the initial evaluator, and the physiotherapist-therapist who will apply the subsequent treatment to ensure blinding, will proceed to randomly assign the subjects to one of the two study groups through a list previously generated with GraphPad software (version 5.01 Graphpad software, Inc. San Diego, California, USA).

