## Outcomes

### Primary outcome

#### Pain intensity

*Visual Analogue Scale (VAS)*. Pain intensity will be measured using a 100 mm visual analog scale where 0 represents ‘no pain’ and 100 the ‘worst pain imaginable’. Participants draw a mark at a point on the line that best reflects the pain they are experiencing at the time of measurement. Higher scores indicate higher pain levels. The sensitivity and specificity of this questionnaire and the acceptability of its psychometric properties have been approved [42].

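### Random measurement order lets painful testing or venepuncture precede the momentary-pain VAS at some visits, and it conflicts with the baseline procedure, which draws blood last

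*Protocol article*

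**What the plan says.** Four statements in the protocol article bear on this.

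- **Order, general rule** (Outcomes, Others): "All the outcome measurements will be assessed in a random order at baseline, at the halfway point of the treatment, post-intervention", and again at one and eight months. The sentence exempts no outcome.
- **Order, procedure** (Interventions): "Once the specific questionnaires and the pressure pain threshold (PPT) at the joints of the elbow and tibialis anterior are measured, a trained professional will" take the blood sample. The same paragraph fixes the time of day: "The blood collection will always take place between 6 p.m. and 7 p.m., to minimize the possible effects of circadian changes".
- **Primary outcome** (Pain intensity): "Participants draw a mark at a point on the line that best reflects the pain they are experiencing at the time of measurement". The section also classes the VAS as a questionnaire: "The sensitivity and specificity of this questionnaire and the acceptability of its psychometric properties have been approved".
- **Algometry site**: Interventions names the elbow and tibialis anterior. Others says "The algometer will be applied to different points in the body (elbow and knee").

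The pressure pain threshold (PPT) is found by raising the pressure until the participant reports pain. Plasma BDNF is a secondary outcome and needs a venous sample. Both are therefore outcome measurements under the general rule. The analysis section uses the baseline value as the covariate in the mixed-model ANCOVA.

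**The concern.** A rating of pain at this moment is exposed to whatever was done to the patient minutes before. Under the general rule, some VAS scores would follow algometry or a needle and others would not, and this could change from visit to visit in the same patient. That adds variation unrelated to chronic pain, both to the follow-up VAS and to the baseline VAS used for adjustment.

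The two sections also cannot both be followed at baseline. One allows the blood sample anywhere in the sequence, and the other places it after the questionnaires and algometry. An assessor working from the article has two instructions for the order and two for the lower-limb algometry site. If different assessors or visits resolved the site differently, the PPT values would not be comparable.

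**Working it through.** **1. The two orders compared**

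| Pair | Others (all visits) | Interventions (initial data collection) |
|---|---|---|
| VAS and blood | either first | VAS first, since it is classed as a questionnaire |
| PPT and blood | either first | PPT first |
| VAS and PPT | either first | both before blood; no order between them is set |

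The firm contradiction concerns the blood sample. It is certain at baseline, which both sections cover. Interventions does not say that its sequence holds at later visits. For VAS and PPT the two sections do not contradict each other, but neither guarantees that the VAS comes first.

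**2. The plan's own sample size**

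Inputs from Sample size: difference 2 VAS points, SD 3.227, d = 2/3.23 = 0.619195, alpha 0.05, power 90%, 1:1 allocation, 15% dropout. The article does not state sidedness.

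- Two-sided two-sample t-test (noncentral t): n = 55.79, so 56 per group, as stated. A one-sided test would need 46, so the plan's figure is two-sided.
- Dropout: 56/0.85 = 65.9, so 66 per group, as stated.
- Power at 56 per group: 90.1% with d = 0.619195, and 90.2% with d = 2/3.227.

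**3. Illustration of the noise**

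The documents give no size for an order effect, so the shift is assumed. Suppose a preceding painful procedure raises the VAS by s points and a proportion p of patients have had one before rating, independently of arm. Then

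added variance = p(1 − p)s², and new SD = √(3.227² + p(1 − p)s²), with 3.227² = 10.41.

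With p = 1/2 and 56 per group:

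| s | Added variance | Share of 10.41 | New SD | Power |
|---|---|---|---|---|
| 0.5 | 0.0625 | 0.6% | 3.237 | 90.0% |
| 1 | 0.25 | 2.4% | 3.266 | 89.5% |
| 1.5 | 0.5625 | 5.4% | 3.313 | 88.6% |
| 2 | 1.00 | 9.6% | 3.378 | 87.4% |

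**4. Sensitivity to p**

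If VAS, PPT and blood are in fully random order, the VAS is first with probability 1/3, so at least one painful procedure precedes it with probability p = 2/3. Then p(1 − p) = 2/9.

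- s = 1: added variance 0.22 (2.1%), power 89.6%.
- s = 2: added variance 0.89 (8.5%), power 87.7%.

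The result hardly changes.

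These figures use the plan's t-test and put the noise in the follow-up score only. They do not model noise in the baseline covariate.

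**The case against.** **The sections can nearly be reconciled.** A sensible team might randomise the order of questionnaires and algometry and then draw blood in its fixed evening window. Random order may have been meant for the questionnaires alone, and the figures cited in that sentence are not visible. This stands as a plausible intention, and it would remove venepuncture before the VAS. The sentence nevertheless says all outcome measurements, and even this reading leaves algometry free to come before the VAS.

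**Random order does not bias the comparison.** This stands. Nothing ties order to arm, and randomising order is a recognised guard against systematic order effects. A reader might infer that the VAS difference would partly reflect an effect of education on reactions to provoked pain. The article does aim to change catastrophizing and coping, but it gives no evidence of such a reaction or of carry-over from a threshold test to the VAS. That inference is conjecture.

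**The shift is invented and the planning SD is generous.** This also stands. The upper assumed shift of 2 points equals the trial's whole target difference. The pilot SDs of 1.29 and 2.61 pool to √[(1.29² + 2.61²)/2] = 2.06, variance 4.24, against a planning variance of 10.41. If the pilot SD were right, adding 1.0 to its variance would still leave power above 99% at 56 per group.

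**The site difference may be loose wording.** Knee may be shorthand for the upper tibialis anterior. A reader might infer that two lower-limb sites will be measured and pooled, but no section says so. What stands is that the two descriptions differ.

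**Within-visit order is operational detail.** An article may omit it. This one states it twice, differently.

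**Conclusion.** The point holds as an inconsistency with a small, avoidable cost to precision. The general rule, read literally, allows the momentary-pain VAS to follow algometry or venepuncture at some visits and not at others. The Interventions section conflicts with that rule on the blood sample, with certainty at baseline only. Neither section puts the VAS before algometry. The lower-limb algometry site is also inconsistent.

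A reader might take Interventions to fix a full sequence of questionnaires, then PPT, then blood. It does not: it lists the first two together and fixes only that blood follows them.

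The consequence is noise in the primary outcome and its baseline covariate, not a demonstrated bias. On an assumed shift of 1 to 2 points in half of patients, power at 56 per group falls from about 90% to between 89.5% and 87.4%. The shift is an assumption without support in the documents, and the true loss may be smaller. The stated sample size reproduces and needs no change on this account. The correction is still worth making, because it settles what the primary outcome measures at every visit and costs almost nothing.

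**What to change.** Reconcile the Interventions section with the last sentence of Others:

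- Take the VAS first at every visit, before algometry and before the blood sample.
- Limit random order to the remaining questionnaires.
- State one fixed order for algometry and blood at all five visits. The blood-last order already in Interventions is acceptable, and nothing here calls for reversing it.
- Name the same lower-limb algometry site in both sections.

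The cost is wording in the protocol and the visit checklist. No extra visit time, staff or participants are needed.

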**Fig 3 pone.0289430.g003:**
[figure not shown]
Flow diagram.

**Fig 4 pone.0289430.g004:**
[figure not shown]
Trial timeline.

**Fig 5 pone.0289430.g005:**
[figure not shown]
SPIRIT figure showing the schedule of enrolment, interventions, and assessments.

#### Participants’ timeline

We have included a schematic diagram outlining the time frame for participant enrolment, interventions, assessments, and visits, as shown in the following figures (Figs 4 and 5).

#### Sample size

The determination of the sample size used a t-test for independent means, calculated using G*Power software (Universität Düsseldorf, Germany). The significance level was set at 0.05, and a power of 90% was targeted. The effect size, assessed by Cohen’s d, was predicted based on a mean difference of 2 points in the Visual Analog Scale (VAS), as it is commonly considered the minimum clinically relevant change in many chronic pain conditions [55], and the pooled standard deviation (SD_pooled). This was derived from the standard deviations of the intervention and control groups in a preliminary study, which were 1.29 and 2.61, respectively.

In recognition of the potential underestimation of standard deviations in the pilot study, the original SD values were adjusted using the Upper Confidence Limit (UCL) method, as described by Whitehead et al. [56], based on Browne’s [57] approach. This adjustment, accounting for a 95% confidence level, yielded an SD of 3.227 using the formula [56, 57]: s_UCL^2 = [k/(X_(1-X,k)^2)] s^2.

Consequently, the effect size (d) was calculated as 0.619195 (derived from 2/3.23). With a 1:1 allocation ratio between groups, G*Power [58] indicated a requisite minimum of 56 subjects per group to detect a 2-point difference in VAS with 90% power. Considering a 15% dropout rate, the final sample size was set at 66 subjects per group, totaling 132 subjects for the study to maintain the desired statistical power.

### Recruitment

#### Allocation

*Sequence generation*, *concealment mechanism*, *and implementation*. Individuals meeting the inclusion criteria will be randomly allocated to one of two treatment arms: (1) POBTE plus exercise or (2) exercise therapy alone. Randomization will be conducted using computer-generated random numbers in block sizes ranging from 8 to 12, accommodating the requirements of the group intervention and ensuring that each group consists of 4 to 6 participants for the intervention to be feasible. The allocation will be concealed in an opaque, sealed envelope. A research assistant will open these envelopes and assign patients to their respective treatment arms. Multiple randomizations will be performed corresponding to the number of intervention-control groups formed. The randomization process will take place after obtaining informed consent and conducting baseline assessments.

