#### Statistics: Outcome

Data analysis will be conducted using the statistical software SPSS version 25.0 (SPSS Inc., Chicago, IL, USA). A descriptive analysis of the demographic characteristics and pain intensity of the sample size will be performed, presenting continuous variables as mean ± standard deviation (SD) and 95% confidence interval (CI), while categorical variables will be presented as number (n) and percentage (relative frequency, %). In instances where quantitative variables follow a non-normal distribution, they will be described using the median and interquartile range.

For the comparison between groups, parametric tests based on the central limit theorem will be chosen, since the sample size of both groups will be greater than 30 [56]. A mixed-model Analysis of Covariance (ANCOVA) will be used including baseline as the covariate, to obtain between-group adjusted mean differences at each follow-up point, controlling for type I error rate using Bonferroni’s correction. The chi-square test will be used for nominal variables. If the criteria for parametric testing cannot be met, robust methods will be applied [57]. A p-value < 0.05 will be accepted as statistically significant.

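### Patients are treated in groups of 4 to 6, but the sample size assumes independent patients and the named ANCOVA has no treatment-group term.

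*Protocol article*

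**What the plan says.** The Allocation section randomises individual patients 1:1 in blocks of 8 to 12. The block size is explained as "accommodating the requirements of the group intervention and ensuring that each group consists of 4 to 6 participants for the intervention to be feasible". It adds: "Multiple randomizations will be performed corresponding to the number of intervention-control groups formed". A block of 8 to 12 split equally yields 4 to 6 patients per arm, which matches the stated group size. The Eligibility criteria section lists two physiotherapists for education and exercise together, without saying how they are divided between arms.

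The Sample size section takes no account of this grouping: "The determination of the sample size used a t-test for independent means". The only allowances are an upward adjustment of the pilot SD and 15% dropout.

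Under Statistics: Outcome, the model is described as follows: "A mixed-model Analysis of Covariance (ANCOVA) will be used including baseline as the covariate". It is to give adjusted differences at each follow-up point with a Bonferroni correction. Baseline is the only covariate named, and no term for session group, therapist or block is mentioned.

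**The concern.** Patients who attend the same sessions may end up with correlated outcomes, through group dynamics, the way a particular course was delivered, or influence on one another. Individual randomisation makes the arms comparable at entry but does not remove correlation that arises during treatment. If part of the outcome variance belongs to the session group, the arm mean varies more than an independent-patients formula allows. A patient-level random effect for repeated visits does not absorb this, because it describes correlation within a patient and not between patients in a group.

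The primary comparison would then carry confidence intervals that are too narrow and a type I error above the nominal 5%. The stated power would also be optimistic relative to its own inputs. There is a practical side: if session-group membership is not recorded during the trial, it may not be recoverable for the analysis.

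**Working it through.** **Inputs from the article.** Sample size section: "The significance level was set at 0.05, and a power of 90% was targeted"; "mean difference of 2 points in the Visual Analog Scale (VAS"; "yielded an SD of 3.227 using the formula"; "the effect size (d) was calculated as 0.619195 (derived from 2/3.23"; 56 per arm before dropout and 66 after it. Allocation section: groups of 4 to 6.

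**Assumed.** ICC of 0.01 to 0.10, because the article gives none. About 13 groups per arm: 66/5 = 13.2. That is 5 per group as randomised, and 56/13 = 4.31 per group among completers.

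**Step 1: reproduce the plan.** A two-sided t-test with d = 2/3.23 = 0.619 and alpha 0.05 (noncentral t) has power 89.6% at 55 per arm and 90.1% at 56. Dropout: 56/0.85 = 65.9, so 66. The plan's arithmetic is right under independence.

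**Step 2: type I error of a test that ignores groups.** With m = 5, the true variance of the arm difference is the naive variance times a factor F:
- all correlation group-specific, both arms clustered: F = 1 + (m−1)·ICC
- one arm clustered: F = 1 + (m−1)·ICC/2
- all correlation shared by both halves of a block: F = 1 + (m−1)·ICC − m·ICC = 1 − ICC

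Type I error is about 2[1 − Φ(1.96/√F)].

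| ICC | Both arms, group-specific | One arm only | All shared by block |
|---|---|---|---|
| 0.01 | F 1.04, 5.5% | F 1.02, 5.2% | F 0.99, 4.9% |
| 0.02 | F 1.08, 5.9% | F 1.04, 5.5% | F 0.98, 4.8% |
| 0.05 | F 1.20, 7.4% | F 1.10, 6.2% | F 0.95, 4.4% |
| 0.10 | F 1.40, 9.8% | F 1.20, 7.4% | F 0.90, 3.9% |

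Simulating an ordinary t-test with 13 groups of 5 per arm agrees within simulation noise: about 5.3%, 5.9%, 7.5% and 9.8% for the first column, and about 5.1% to 7.4% for the second. The third stays below 5%.

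**Step 3: power.** Among completers, the design effect is DE = 1 + (4.31 − 1)·ICC and the effective n per arm is 56/DE. Power comes from the noncentral t with noncentrality 0.619·√(n_eff/2), taking all correlation as group-specific in both arms. Three choices of degrees of freedom (df) are shown: 110 (2·56 − 2, the plan's test), 24 (26 groups − 2, group as a random effect) and 12 (26 groups − 13 blocks − 1, block also fixed).

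| ICC | DE | n_eff | Power, df 110 | Power, df 24 | Power, df 12 |
|---|---|---|---|---|---|
| 0 | 1.000 | 56.0 | 90.1% | 88.2% | 85.2% |
| 0.01 | 1.033 | 54.2 | 89.2% | 87.1% | 84.1% |
| 0.02 | 1.066 | 52.5 | 88.2% | 86.1% | 82.9% |
| 0.05 | 1.165 | 48.1 | 85.3% | 82.9% | 79.6% |
| 0.10 | 1.331 | 42.1 | 80.4% | 77.8% | 74.2% |

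The df 110 column isolates the effect of clustering. The further drop in the other columns is the price of fewer degrees of freedom and is already present at ICC 0.

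**The case against.** Several points on the other side stand.

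- **Shared block effects cancel.** Calendar time, or a therapist who treats both arms, affects both halves of a block and drops out of the contrast. A reader might infer that any shared circumstance pushes type I error above 5%. The last column of Step 2 shows that this part makes the naive test conservative. How the correlation divides between group and block is unknown.
- **Control-arm grouping is inferred.** The reference to intervention-control groups and the block arithmetic point to groups in both arms. The descriptions of the two interventions do not say that exercise is delivered in groups, and the exercise checklist is not shown.
- **Power has offsets.** The SD of 3.227 is well above the pilot's pooled value, √[(1.29² + 2.61²)/2] = 2.06 with equal arms. The sizing also ignores baseline adjustment. At an assumed baseline correlation of 0.5, the SD shrinks by √0.75, and power with df 24 is about 92% at ICC 0.05 and 88% at ICC 0.10. The Bonferroni correction pulls the other way. A reader might infer that the trial is underpowered and must be enlarged; the article does not support that. None of these offsets corrects the standard error.
- **The model may be completed elsewhere.** The article says mixed-model without listing random effects, and an analysis plan that is not shown could include one for session group. That would repair the standard error but leave the independence-based sample size as stated.

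**Conclusion.** The inconsistency is real: the article fixes delivery in groups of 4 to 6, sizes the trial as if patients were independent, and names an analysis model without a group term. Its size rests on an ICC that the article does not give.

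Over an assumed 0.01 to 0.10, type I error runs from about 5.3% to 9.8% in the least favourable case and from about 5.1% to 7.4% with one arm clustered. It falls below 5% if the correlation belongs wholly to the block. The design effect alone takes power from 90% to between 89% and 80% on the plan's t-test inputs. Near an ICC of 0.01 both effects are minor.

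The article therefore does not establish that the type I error must exceed 5%, or that the planned ANCOVA has less than 90% power. What it does show is that the validity of the error bars depends on an unstated assumption of no session-group correlation. This should be fixed, but it does not undermine the design.

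**What to change.** 1. Record a session-group identifier for every patient as the groups are formed, and state whether the control exercise is given in groups.
2. Add a random intercept for session group to the mixed model, with small-sample degrees of freedom such as Satterthwaite. If the control exercise is not given in groups, fit this term in the education arm only.
3. Restate the power over a declared ICC range, using 1 + (m − 1)·ICC and the degrees of freedom of the model actually chosen: about 24 with 13 groups in each arm, about 12 if block is also a fixed factor. Any allowance for baseline adjustment should be stated with its assumed correlation.

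The cost is one identifier, one model term, somewhat wider confidence intervals and a lower stated power. No larger sample is required.
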